#### AMR

We plan to monitor 20 randomly selected CSIs per arm and 3 randomly selected communities per CSI, giving a total of 60 communities per arm. Within each community, 20 children will be randomly selected from the prior census to receive sample collections following procedures described above.Nasopharyngeal samples. A total of 120 communities (60 per arm) will provide approximately 80% power to detect a 7% absolute increase in the prevalence of macrolide-resistant pneumococcus isolates between arms. This assumes a 10% baseline prevalence of macrolide resistance, a community-level ICC of 0.045 estimated from MORDOR I 24-month data, and an alpha of 0.05 [12].Rectal samples: A total of 120 communities (60 per arm) will allow 80% power to detect a 1.4-fold increase in community mean normalized read number of genetic determinants of resistance to macrolides in rectal samples. This assumes an estimated ICC of 0.02 from the MORDOR I 24-month data, a standard deviation of 3.1 (on the logarithmic scale), and an alpha of 0.05 [12].

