#### Under-5 mortality rate (U5MR)

We estimate that monitoring a total sample of 200 CSIs, evenly split between MDA and delayed, would have 80% power to detect a reduction in the U5MR of 6.6 per 1000 live births. At 90% power, the reduction in U5MR is approximately 7.7 per 1000 live births. These estimates are based on a sample size equation for a t-test of cluster-level means. We assumed an alpha of 0.05 and a standard deviation of 16.6 in the CSI-level U5MR, which was estimated from the MORDOR Niger trial 5-year birth history substudy, which provided the most recent U5MR estimates available [25].

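### The 80% power stated for a 1.4-fold rise in rectal macrolide-resistance load does not follow from the inputs printed beside it on any log base

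*Protocol article*

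**What the plan says.** The AMR part of Sample size and power takes 20 CSIs per arm and 3 communities per CSI, "giving a total of 60 communities per arm". On the children it says: "Within each community, 20 children will be randomly selected from the prior census to receive sample collections". The Antimicrobial resistance section under Outcome assessments gives the same 20 children per community.

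For rectal samples the result is that these 120 communities "will allow 80% power to detect a 1.4-fold increase in community mean normalized read number of genetic determinants of resistance to macrolides". The assumptions follow: "This assumes an estimated ICC of 0.02 from the MORDOR I 24-month data", and "a standard deviation of 3.1 (on the logarithmic scale), and an alpha of 0.05". Neither the base of the logarithm nor the sidedness of the test is given. No baseline adjustment, other variance reduction or sample loss is mentioned for this calculation.

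Rectal resistance load is listed among the primary AMR outcomes for both trials. The opening of Sample size and power carries the Trial 1 calculations over to Trial 2.

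**The concern.** The article prints a full set of inputs and a result, and the two disagree. This differs from a detail left to a longer document, because a reader who uses the printed numbers cannot arrive at the printed power.

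The Ministry of Health committee is to weigh resistance against mortality benefit when deciding whether to continue, expand or stop the program. The stated detectable rise tells it how much reassurance a null rectal result carries. If the scale is natural log, a true 1.4-fold rise would be missed about 38% of the time instead of 20%. If it is log2, the design is more sensitive than claimed. The committee cannot tell which holds.

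**Working it through.** **Sidedness.** The mortality calculation in the same section shows the convention: "We assumed an alpha of 0.05 and a standard deviation of 16.6 in the CSI-level U5MR", with 100 CSIs per arm. The standard error is 16.6 × √(2/100) = 2.348.
- Power at 6.6 per 1000: Φ(6.6/2.348 − 1.96) = Φ(0.85) = 80%.
- Power at 7.7 per 1000: Φ(7.7/2.348 − 1.96) = Φ(1.32) = 91%.

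Both agree with the article's 80% and 90% under a two-sided 0.05 test. A one-sided test would give Φ(2.811 − 1.645) = 88% at 6.6. Two-sided is therefore taken as the convention.

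**Rectal inputs (AMR part of Sample size and power).** 60 communities × 20 children = 1200 per arm; ICC 0.02; SD 3.1 in log units; two-sided alpha 0.05.

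- Design effect: 1 + (20 − 1) × 0.02 = 1.38.
- Effective number per arm: 1200/1.38 = 869.6.
- Standard error of the difference: 3.1 × √(2/869.6) = 0.1487.
- Difference detectable at 80% power: (1.960 + 0.842) × 0.1487 = 0.4165 log units.
- Power at 1.4-fold: Φ(log 1.4/0.1487 − 1.96).

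| Log base | log 1.4 | Power at 1.4-fold | Fold detectable at 80% power |
|---|---|---|---|
| natural | 0.3365 | 62% | 1.52 |
| 2 | 0.4854 | 90% | 1.33 |
| 10 | 0.1461 | 16% | 2.61 |

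On natural logs a noncentral t with 118 degrees of freedom gives 61%, so the normal approximation is not the cause.

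**Other readings of the SD (natural logs).** SD taken as within-community: 61%. 3.1 taken as a variance: 98%. 3.1 taken as the SD of community means: 3.1 × √(2/60) = 0.566, power 9%. None gives 80%.

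**Departures from the stated inputs (natural logs unless noted).**
- ICC omitted: SE 3.1 × √(2/1200) = 0.1266; detectable 1.43-fold; power at 1.4-fold 76%.
- One-sided 0.05 with the ICC: detectable 1.45-fold; power at 1.4-fold 73%.
- 40 children per community with the ICC: design effect 1 + 39 × 0.02 = 1.78; effective number 2400/1.78 = 1348; SE 0.1194; detectable 1.40-fold; power 80.5%.
- Log2 with half of the 0.02 shared across the three communities of a CSI: design effect 1 + 19 × 0.02 + 40 × 0.01 = 1.78; with 38 degrees of freedom, detectable 1.40-fold.

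The last two meet the published figure, but each needs an input the article does not contain. The third contradicts the 20 children stated in two places.

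**Direction of CSI-level correlation.** CSIs are randomized, with three sampled communities in each. As a bounding assumption, let the whole 0.02 act between any two children of the same CSI. The design effect is then 1 + 59 × 0.02 = 2.18 and the effective number is 1200/2.18 = 550.5. The detectable rise (normal approximation) becomes 1.69-fold on natural logs or 1.44-fold on log2, against 1.52 and 1.33 with none.

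**The case against.** The strongest objection is that the direction of the error is unknown. On log2 the printed inputs give 90% power at 1.4-fold, so the claim would be conservative and there would be no shortfall. That stands. A reader might infer that the trial is underpowered for this outcome, or that it should not be described as powered for 1.4-fold. The article supports neither without the base.

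A reader might also infer that the ICC was left out, since dropping it on natural logs gives 1.43-fold, which rounds to 1.4. That is a guess. Power at 1.4-fold is then 76%, a one-sided test also rounds to 1.4, and 40 children per community fits better than either.

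Nor does the article support replacing 1.4-fold with a value such as 1.6- to 1.7-fold to allow for CSI clustering. It gives no CSI-level ICC, and under one assumed split of the 0.02 log2 returns 1.40-fold.

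Finally, the article condenses a longer protocol that may state the base, sidedness and formula. Their absence alone would be no finding. What remains is that the printed inputs and the printed result disagree on every base.

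**Conclusion.** The rectal power statement is a misstated figure. From the printed 60 × 20 children per arm, ICC 0.02, SD 3.1 and two-sided 0.05, power at 1.4-fold is 62%, 90% or 16% on natural, base-2 or base-10 logs. The corresponding 80%-detectable rises are 1.52-, 1.33- and 2.61-fold. Rounding does not bridge the gap on natural logs or log10. On log2 the result rounds to 1.3.

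This rests on reading 3.1 as the SD of individual children's log values and on the two-sided convention inferred from the mortality calculation. A shortfall in power exists only if the scale is natural log or log10. The cause of the mismatch cannot be determined from the article. Correlation at CSI level would make the detectable rise larger on any base, by an amount that is an assumption.

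**What to change.** In the rectal-sample sentence, state the log base, the sidedness and the number of children per community used in the calculation, and make the result agree with them. With the inputs as printed, the restated figure is:
- natural logs: about 1.5-fold at 80% power, or 62% power at 1.4-fold;
- log2: about 1.33-fold at 80% power, or 90% power at 1.4-fold;
- log10: about 2.6-fold at 80% power, or 16% power at 1.4-fold.

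If another number of children or another ICC was used, correct that input and reconcile it with the 20 children given in both the sample-size and the outcome-assessment sections. Add one sentence saying that randomization is by CSI with three communities in each, that correlation within a CSI would enlarge the detectable rise, and what value was assumed. The cost is a corrected sentence or two. The sample and the design stay as they are.

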#### Implementation outcomes

Sample size calculations were conducted for the coverage evaluation surveys. The surveys will be conducted in a randomly selected subset of 3 CSIs per region among the CSIs after each MDA. Within each CSI, 7 communities will be randomly selected to participate in the survey. We estimate that including approximately 2100 households per region will allow us to estimate caregiver-reported coverage of 70% ± 5% at the region level, assuming an average of 100 households per community—based on AVENIR I, a design effect of 4 based on guidance from the WHO, an alpha of 0.05, and non-response of 10% [3, 21].

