#### Implementation outcomes

The RE-AIM framework was used to define implementation outcomes for evaluation (Table 3) [19, 20]. The following additional data collection activities will take place to measure these outcomes:Coverage and coverage equity. Treatment coverage will be assessed in several ways. CHWs will record key information about each MDA on paper data collection forms, including the number of treated children, adverse events experienced, and the number of days required for the distribution. Administrative coverage will be estimated using current estimates of the under-5 population from CSIs as the denominator and the number of children treated in each MDA according to the CHW data collection form as the numerator. Administrative coverage will be used for official reporting for all CSIs. Census coverage will be calculated using estimated eligible population denominators available from the pregnancy histories conducted in the monitoring CSIS. Administrative and census coverage will be compared to determine the validity of the administrative coverage estimates.Coverage evaluation surveys will be conducted in a randomly selected subset of CSIs to validate coverage estimates using caregiver self-report, to identify subgroups with low coverage to evaluate coverage equity, to understand reasons for low coverage, and to compare outcomes of different implementation strategies. Survey instruments will be developed based on standardized questionnaires used for neglected tropical disease program monitoring according to WHO guidance [21], and implementation strategies will be assessed using versions of the Acceptability of Intervention Measure, Intervention Appropriateness Measure, and Feasibility of Intervention Measures that have been modified to ensure cultural appropriateness [16]. Trained data collectors fluent in local languages will visit every household in selected CSIs and conduct the survey among caregivers of children eligible for the program after obtaining verbal informed consent. Surveys will take place within 1 week of the most recent MDA.In-depth interviews will be conducted after 2 and 4 years in a random sample of caregivers stratified by participation in the program as well as a random sample of CHWs and CSI leaders to identify barriers and facilitators to participation and implementation along with implementation strategies to improve uptake. Interview guides will be developed using the Consolidated Framework for Implementation Research (CFIR) [18]. Trained local interviewers fluent in relevant languages will conduct semi-structured interviews in private locations after obtaining verbal informed consent. Interview recordings and notes will be used for rapid qualitative analysis to immediately summarize each interview according to pre-defined domains, which will then be distilled into a matrix organized by domain and interviewee for analysis [22]. The first 5 interviews will be summarized by the group of interviewers as part of training to achieve consensus on the approach.Process mapping. Process mapping will be used to identify the flow of inputs required to achieve high MDA coverage, along with information on which aspects of the intervention are adaptable, and which are key determinants of high coverage. Following methods used in other MDA settings [23], we will use routine workflow tracking in the same CSIs selected for coverage evaluation surveys to record data on key activities during each round of MDA, including drug supply chain, training, sensitization, and the MDA itself. After 2 years, we will use coincidence analysis to identify any necessary and/or sufficient combinations of intervention activities that resulted in high MDA coverage [24].Costs and cost-effectiveness. Routine expenses will be tracked in all CSIs to monitor overall program costs, costs of program components (training, sensitization, delivery, administrative), costs per district, and costs per dose delivered. Incremental cost-effectiveness of the intervention compared to standard of care will be estimated using program costs, with effectiveness outcomes including measured mortality and estimated DALYs to calculate cost per death averted and cost per DALY averted.Fidelity. We will monitor CHW adherence to the intervention protocol using two methods: local CSI leaders will supervise CHWs in nearby communities according to their standard practice, and the study team will monitor fidelity to the protocol using standardized checklists in the same random sample selected for coverage evaluation surveys. These checks ensure the proper execution of program procedures, including eligibility assessment, dosing, adverse event monitoring, and data collection.

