Limitations of this design include the lack of a placebo control, which increases the potential for bias. However, as multiple prior placebo-controlled trials have demonstrated the efficacy of this intervention and eligible countries are ready to move to large-scale program implementation, placebo is no longer warranted. In addition, all eligible communities in Niger receive multiple community-based health campaigns from the same CHWs each year, limiting concerns of a Hawthorne effect. The design does allow for masking of all outcome assessors, reducing the risk of bias. Another potential limitation involves statistical power. As mortality is declining over time outside of this intervention, and heterogeneity in outcomes may be greater compared to prior studies given the large scale of the implementation, the trial could have less power to detect effects than anticipated based on current assumptions. Power calculations for this trial used data from the MORDOR and AVENIR I trials, which include the most recent population-based mortality data available in Niger from multiple regions to address this concern. Finally, the shift from a controlled trial setting to a real-world program will involve changes in the implementation of the program itself which could impact the ability to detect effects, as there will likely be more variation in program delivery across settings and the program may see lower and more heterogenous MDA coverage than the prior trials. Close monitoring of coverage and factors contributing to coverage heterogeneity were included in the trial design to allow for such evaluation.

AVENIR II will provide evidence on mortality, AMR, implementation, and safety outcomes after large-scale programmatic delivery of azithromycin MDA for child survival in Niger. Results from this trial will support program-related decision-making in Niger and elsewhere. The adaptive platform design provides a flexible approach that allows for this monitoring and enables the evaluation of other community interventions over time.

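### The region-level coverage precision of ±5 points per survey round is not supported by a first stage of three CSIs per region

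*Protocol article*

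**What the plan says.** The design and the precision claim are in the protocol article under Sample size and power, Implementation outcomes. The first stage is: "The surveys will be conducted in a randomly selected subset of 3 CSIs per region among the CSIs after each MDA". The second stage is: "Within each CSI, 7 communities will be randomly selected to participate in the survey". The household figure follows from "assuming an average of 100 households per community", so a region contributes 3 × 7 × 100 = 2100 households. The claim is: "We estimate that including approximately 2100 households per region will allow us to estimate caregiver-reported coverage of 70% ± 5% at the region level", with a design effect of 4 attributed to WHO guidance, alpha 0.05 and 10% non-response. No between-CSI variance or intracluster correlation (ICC) for coverage is given.

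Two other places bear on this. Under Outcome assessments, Implementation outcomes, data collectors "will visit every household in selected CSIs and conduct the survey among caregivers of children eligible for the program", which is not a sample of 7 communities. In the Discussion, the authors warn that "the program may see lower and more heterogenous MDA coverage than the prior trials".

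**The concern.** The CSI is the first-stage unit, and Table 2 lists 192 to 267 CSIs in each of the four trial regions. Three of them have to stand for the whole region in each round. However many households are visited, differences in coverage between CSIs are averaged over three units only, and any variance estimated from those units has 2 degrees of freedom. A single design effect of 4 hides this, because it says nothing about how much of the clustering arises between CSIs.

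The surveys serve to validate coverage by caregiver report, to find subgroups with low coverage and to explain why coverage is low. If a regional figure is read as accurate to 5 points when its real uncertainty is 9 points or more, a difference between regions or rounds could be taken as real when it reflects only which three CSIs were drawn.

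**Working it through.** **Inputs from the article.** Coverage p = 0.70, so p(1−p) = 0.21; target half-width d = 0.05; design effect (DEFF) 4; non-response 10%; 3 CSIs, 21 communities and 2100 households per region. Respondents: 2100 × 0.9 = 1890 per region, 630 per CSI, 90 per community. A two-sided 95% interval is assumed.

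**1. The plan's own figure.** Simple random sampling needs 1.96² × 0.21/0.05² = 323 households. Times 4 gives 1291; divided by 0.9 gives about 1434. The planned 2100 is the field layout and exceeds this. With 1890 respondents, SE = √(0.21 × 4/1890) = 2.11 points, and 1.96 × 2.11 = ±4.1 points. On its stated inputs the claim is met with a margin.

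**2. What DEFF 4 implies about CSIs.** With DEFF = 1 + (m − 1) × ICC and m = 630, ICC = 3/629 = 0.0048. The between-CSI SD is √(0.0048 × 0.21) = 3.2 points. This is an upper bound, because it assigns all clustering to the CSI. If communities within a CSI differ with an assumed ICC of 0.02, they use (90 − 1) × 0.02 = 1.78 of the available 3, leaving a between-CSI SD of about 2.0 points. With 0.03 it is about 1.0 point. If DEFF 4 was meant at community level, it equals an ICC of 3/89 = 0.034 and leaves nothing for CSIs.

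**3. Where ±5 fails with the normal multiplier.** The largest tolerable DEFF is (0.05/1.96)² × 1890/0.21 = 5.86. The corresponding CSI-level ICC is 4.86/629 = 0.0077, a between-CSI SD of 4.0 points.

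**4. CSI as sampling unit.** With 3 CSIs there are 2 degrees of freedom and t = 4.303. Still granting DEFF 4, the half-width is 4.303 × 2.11 = ±9.1 points. To reach ±5 with this multiplier, DEFF may be at most (0.05/4.303)² × 1890/0.21 = 1.22, a between-CSI SD of about 0.8 points. A finite-population correction barely changes this: with 192 CSIs the factor is √(1 − 3/192) = 0.99.

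**5. CSI sampling alone, at assumed SDs.** The half-width is multiplier × SD/√3.

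| Assumed between-CSI SD (points) | z = 1.96 | t, 2 df |
|---|---|---|
| 5 | ±5.7 | ±12.4 |
| 8 | ±9.1 | ±19.9 |
| 10 | ±11.3 | ±24.8 |

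**6. Number of CSIs needed.** Keep 1890 respondents and assume no clustering of communities within CSIs. The half-width with k CSIs is t(k − 1) × √(SD²/k + 0.21 × 10⁴/1890), in points. At SD 5, 7 CSIs give ±5.3 and 8 give ±4.9. At SD 10, 21 CSIs give ±5.06 and 22 give ±4.9. Clustering within CSIs would raise these counts.

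**7. Pooling one round over the four regions.** There are 12 CSIs, 12 − 4 = 8 degrees of freedom, t = 2.306 and 4 × 1890 = 7560 respondents. With regions weighted equally (an approximation), DEFF 4 gives 2.306 × √(0.21 × 4/7560) = ±2.4 points. Using √(SD²/12 + 0.21 × 10⁴/7560), SDs of 5, 8 and 10 give ±3.5, ±5.5 and ±6.8.

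**The case against.** The best defence is that the article's arithmetic works: on its own inputs 2100 households are more than enough. That stands. A reader might infer from 2100 against 1434 that the sample size was miscalculated. It was not; the difference is a conservative margin.

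A second defence is that the between-CSI SDs of 5 to 10 points are assumptions. The article gives no figure, and the Discussion says only that coverage may be more heterogeneous, without locating that variation between CSIs of one region. This also stands. A reader might infer that three CSIs cannot deliver ±5. The documents do not show that; it depends on how much CSIs differ.

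Third, the multiplier with 2 degrees of freedom applies only when the variance is estimated from one region's three CSIs in one round. If DEFF were truly known to be 4, about 95% of estimates would fall within 4.1 points of the true value. The article details statistical methods for the primary mortality and AMR outcomes only, so how coverage intervals will be built is not stated, and one may not infer that they will be computed wrongly. What remains is that a DEFF of 4 is itself demanding at CSI level, and the result in step 3 does not depend on the t multiplier.

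Fourth, the stakes are limited. This is an implementation outcome. Administrative coverage is checked against census coverage in the monitoring CSIs, independently of this survey, and the survey is repeated after each MDA.

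**Conclusion.** The point holds in a conditional form. The stated region-level precision of ±5 points per round is reached only if CSIs within a region scarcely differ: a between-CSI SD of up to about 4 points with the normal multiplier and no community clustering within CSIs, or below about 1 point if the variance is estimated from the three CSIs. At the plan's own design effect, the interval with the CSI as sampling unit is about ±9 points. The wider figures, up to ±25, rest on assumed SDs and show a range, not an expected result. More households in the same three CSIs would not help.

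Separately, surveying every household of a selected CSI conflicts with sampling 7 communities, since the article puts an average catchment at about 20. This is a minor inconsistency in wording that affects workload and sample definition. It is not evidence on precision.

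The point deserves correction but does not touch the primary outcomes.

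**What to change.** **Restate the claim.** Withdraw the region-level ±5%, or replace it with the half-width obtained with the CSI as primary sampling unit, shown over a stated range of between-CSI SD. Claim tighter precision only when pooled over the 12 CSIs or over rounds, again with the range: by step 7, even the pooled figure exceeds ±5 at an assumed SD of 8 points. Pooling over rounds adds degrees of freedom only if CSIs are drawn afresh, so say whether they are. This costs a few sentences.

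**Optionally, spread the communities.** The same 21 communities per region could be taken from more CSIs. About 8 CSIs are needed at an assumed SD of 5 points. About 22 are needed at 10 points, one more than the 21 communities allow. No additional households are needed at 8 CSIs, but there is a cost. Travel rises within the one-week window after each MDA, and process mapping and fidelity checks use the same CSIs, so they would either expand or need their own subsample.

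**Reconcile the two descriptions.** Bring the household visit described under Outcome assessments into line with the sample of 7 communities per CSI described under Sample size and power.
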